### 2.7 Data collection

Demographic data [including age, sex, race, height, weight, and body mass index (BMI)] and baseline characteristics (including comorbidities, preoperative medications, baseline MAP and HR values, and ASA status) will be collected prior to the procedures. The primary and secondary outcome measures and other perioperative data will be documented by a trained independent investigator blinded to group assignment. All raw data will be recorded on the Case Report Forms. The lead investigator will be responsible for the completeness and accuracy of data.

### 2.8 Safety monitoring

Propofol is widely used for sedation in various clinical settings, and emerging literature has demonstrated the use of fospropofol in patients undergoing gastrointestinal endoscopy or other clinical procedures (Cohen et al., 2010; Candiotti et al., 2011; Abdelmalak et al., 2012; Bergese et al., 2013; Wu et al., 2021). Thus, serious adverse events related to the interventions in this trial are less likely to occur. However, in case of a serious adverse event, the attending anesthesiologist will provide immediate clinical management and such an event should be reported to the principal investigator and the Institutional Review Board. They will decide whether the unmasking process of group allocation should be done.

### 2.9 Sample size evaluation

The study is designed as a non-inferiority trial with a non-inferiority margin (δ) of 8% in terms of the success rate (Luo et al., 2022; Zhong et al., 2023). At a power of 80%, a one-sided alpha of 0.025, and assuming that the success rate of gastrointestinal endoscopy after fospropofol or propofol administration is both 95%, a total of 234 patients are calculated using PASS software (version 2021, NCSS, United States). Together with an anticipated drop-out rate of 10%, a total of 256 patients (128 patients in each group) will be required for this trial.

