### 2.10 Data management and statistical analysis

Statistical analysis in this trial will be performed using SPSS 25 (SPSS Inc., Chicago, Illinois, United States). Continuous variables are presented as the mean ± standard deviation (SD) or median with the upper and lower quartiles, whereas categorical variables are presented as frequencies and percentages. A P-value <0.05 is considered statistically significant. For the primary efficacy outcome, the difference in gastrointestinal endoscopy success rate between fospropofol and propofol groups and the corresponding two-sided 95% confidence intervals (CIs) will be calculated. Non-inferiority between fospropofol and propofol is concluded if the lower limit of the two-sided 95% CI of the difference in success rate between fospropofol and propofol groups exceeds the non-inferiority margin (−8%). The success rates of gastrointestinal endoscopy will be compared between the fospropofol and propofol groups using the Chi-square test or Fisher’s exact test. The Shapiro-Wilk’s test will be used to assess the data distribution. For comparison of secondary efficacy outcomes, the Cochran–Mantel–Haenszel (CMH) test or Fisher’s exact test will be used to compare the categorical variables between two groups, while a t-test (normal distribution) or Mann-Whitney U test (non-normal distribution) is used to compare continuous variables, as appropriate. The incidence of AEs and drug-related AEs between the two groups will be compared using a chi-square test or Fisher’s exact test. In addition, the further interaction analysis across the subgroups, including age (65–79 years vs. ≥ 80 years), history of cardiovascular, renal, hepatic, and pulmonary diseases (yes vs. no), as well as interventional therapeutic endoscopic procedures (yes vs. no), will be carried out using a logistic regression model to adjust the study outcomes for above-mentioned potential confounding factors. All randomly assigned patients who receive at least one dose of the study medication will be included in the full analysis set (FAS) according to the intention-to-treat (ITT) principle, and at least one evaluable efficacy outcome is used for the analysis of all efficacy outcomes and baseline characteristics of patients. The safety set (SS), which includes all patients based on the “as treated” principle, will be used for the analysis of safety outcomes. Since the anticipated protocol violation will be uncommon and missing data will be supposed to be missing at random, the interim analysis or imputation for missing data are not performed in this trial.

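### The stated 80% power and one-sided 0.025 error do not hold together at 234 or 256 patients: a Wald interval exceeds the error, and a Newcombe or score interval gives 72 to 77% power

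*Protocol article*

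**What the plan says.** Section 2.9 sets the design: "The study is designed as a non-inferiority trial with a non-inferiority margin (δ) of 8% in terms of the success rate". It gives the operating characteristics as "At a power of 80%, a one-sided alpha of 0.025", with 95% success assumed in both arms, and reports the result: "a total of 234 patients are calculated using PASS software". It then allows for losses: "Together with an anticipated drop-out rate of 10%, a total of 256 patients (128 patients in each group) will be required for this trial".

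Section 2.10 states how the primary outcome is judged. The difference in success rates is estimated, and "the corresponding two-sided 95% confidence intervals (CIs) will be calculated". Non-inferiority is concluded if the lower limit lies above −8%. The article names neither the interval method nor the PASS procedure. Section 2.10 also says that missing data are not imputed and that the efficacy analysis needs an evaluable outcome.

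**The concern.** The normal approximation behind an unpooled sample size formula is weak when success is near 95%. Only about six failures per arm are expected (117 × 0.05 = 5.85), and the variance estimated from the observed proportions is often too small. The resulting interval can then be too narrow. Its lower limit clears −8% too often when fospropofol really is 8 points worse, and the nominal power is bought partly with that excess error.

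The conclusion of the trial is a non-inferiority claim, so the false-positive rate at the margin is the quantity that section 2.9 undertakes to hold at 0.025. If it is not held, the claim is weaker than stated. If it is held by using a better interval, the trial has less chance of success than stated. The drop-out allowance raises a smaller question: whether 256 leaves the 234 that the calculation requires.

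**Working it through.** **Inputs (section 2.9).** Margin 0.08; success 0.95 in both arms; one-sided alpha 0.025 (z = 1.960); power 0.80 (z = 0.842); 1:1 allocation; 10% drop-out; 256 randomised.

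**1. Reproducing 234.** The unpooled normal formula gives

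n per arm = (1.960 + 0.842)² × 2 × 0.95 × 0.05 / 0.08² = 116.5, rounded up to 117, so 234 in total.

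The plan's figure is reproduced. The approximate power at 117 per arm is 80.2%. The score (Farrington-Manning) formula with restricted variance gives 145.1, so 146 per arm. The 234 therefore corresponds to a Wald-type calculation.

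**2. Exact behaviour of the decision rule.** For each n per arm, every pair of success counts was enumerated. The rule of section 2.10 (lower 95% limit above −8%) was applied to each pair, and the binomial probabilities of the passing pairs were summed. Power is taken at 95%/95%. Error is taken on the margin: fospropofol 87% against propofol 95% (the planning rate), and 91% against 99%.

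| n per arm | Interval | Power 95%/95% | Error 87% vs 95% | Error 91% vs 99% |
|---|---|---|---|---|
| 115 | Wald | 79.5% | 3.42% | 4.46% |
| 115 | Newcombe | 72.1% | 2.35% | 1.96% |
| 115 | Miettinen-Nurminen | 72.1% | 2.35% | 1.96% |
| 117 | Wald | 80.9% | 3.25% | 5.01% |
| 117 | Newcombe | 72.2% | 2.43% | 1.77% |
| 117 | Miettinen-Nurminen | 71.5% | 2.18% | 1.77% |
| 128 | Wald | 83.3% | 3.08% | 5.12% |
| 128 | Newcombe | 77.3% | 2.48% | 1.82% |
| 128 | Miettinen-Nurminen | 76.0% | 2.29% | 1.81% |

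Other choices do not change the picture:
- The pooled-variance version behaves like Wald (80.9% power, 3.25% error at 117).
- A continuity-corrected Wald interval gives 72.2% power with 1.90% error at 117, and 76.0% with 2.02% at 128.
- Agresti-Caffo lies between: 77.1% power with 2.65% error at 117, and 81.5% with 2.78% at 128.

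None of the intervals tried gives both 80% power and an error of at most 0.025 at 115, 117 or 128 per arm.

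**3. Drop-out step.**
- Required for 234 evaluable after 10% loss: 234 / 0.9 = 260.
- Left from 256 after 10% loss: 256 × 0.9 = 230.4, so 230, or 115 per arm.
- Loss that 256 tolerates: 1 − 234/256 = 8.6%.
- A likely origin of 128: 117 × 1.1 = 128.7, truncated. Multiplying by 1.1 is not the same as dividing by 0.9.
- Effect on approximate Wald power: 80.2% at 117 per arm, 79.5% at 115.

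**The case against.** The strongest reply is that nothing was miscalculated: 234 is what a standard formula returns, and exact Wald power at that size is 80.9%. That stands, and the point is not that the 234 is an arithmetic error.

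A second reply is that an article commonly leaves the interval method to the SAP, which is not shown. That also stands, and the omission by itself is no defect. But it does not rescue section 2.9. Whichever of the intervals above an SAP names, one of the two stated figures fails.

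Third, 72% is not the only possible figure. It depends on the interval and on the number analysed. Treatment and primary outcome fall in one session, so losses may be small; with all 256 analysed, power is 76 to 77%. If success runs higher than planned, power recovers: at 97% in both arms, Newcombe at 117 per arm gives 85%. The Newcombe and score intervals are also not perfect. Over other control rates their error peaks at about 0.026 to 0.027.

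Three stronger readings are tempting and are not supported:
- A reader might infer that the error is doubled. That is so only near 91% versus 99%; at the planning rate the excess is about 0.8 percentage points.
- A reader might treat 256 instead of 260 as a serious shortfall. It costs less than one point of power.
- A reader might infer that the added comparison ("The success rates of gastrointestinal endoscopy will be compared between the fospropofol and propofol groups using the Chi-square test" or Fisher's exact test) can contradict the primary conclusion. With 112/117 against 117/117, the Wald lower limit is −7.9% and the chi-square P is 0.024. But five failures in all give an expected count of 2.5 per arm, which would ordinarily select Fisher's test (P = 0.06). Section 2.10 also makes the confidence limit the only criterion for non-inferiority, and being non-inferior yet different is not a contradiction. There is no case for removing that test.

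**Conclusion.** The concern holds in a limited form. Section 2.9 pairs 80% power with a one-sided error of 0.025, and at the planned size the pair is not achieved. With a Wald interval the power is met, but the error is about 3.3% at the planning rates and about 5% at 91% versus 99%. With a Newcombe or Miettinen-Nurminen interval the error is at or below 0.025 at those rates, but power is about 72% with 230 to 234 evaluable and 76 to 77% with 256.

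These figures assume 95% true success in both arms, equal arms, and the −8% rule as written. Which of the two shortfalls applies depends on an interval method that the article does not name. The drop-out inconsistency is real but minor. The point should be corrected before analysis; it does not make the trial uninterpretable.

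**What to change.** In section 2.10, name the Miettinen-Nurminen or the Newcombe two-sided 95% interval as the one used for the primary non-inferiority decision.

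In section 2.9, restate the allowance and the power, for example: 256 randomised allows 8.6% loss for 234 evaluable; 230 remain if 10% are lost; exact power with the named interval, at 95% success in both arms, is about 72% with 230 to 234 evaluable and 76 to 77% with all 256.

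This changes wording only and requires no extra enrolment. The cost is a less favourable stated power. In return, the declared error is essentially held for the non-inferiority claim. The chi-square or Fisher comparison can stay.

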### 2.10 Data management and statistical analysis

Statistical analysis in this trial will be performed using SPSS 25 (SPSS Inc., Chicago, Illinois, United States). Continuous variables are presented as the mean ± standard deviation (SD) or median with the upper and lower quartiles, whereas categorical variables are presented as frequencies and percentages. A P-value <0.05 is considered statistically significant. For the primary efficacy outcome, the difference in gastrointestinal endoscopy success rate between fospropofol and propofol groups and the corresponding two-sided 95% confidence intervals (CIs) will be calculated. Non-inferiority between fospropofol and propofol is concluded if the lower limit of the two-sided 95% CI of the difference in success rate between fospropofol and propofol groups exceeds the non-inferiority margin (−8%). The success rates of gastrointestinal endoscopy will be compared between the fospropofol and propofol groups using the Chi-square test or Fisher’s exact test. The Shapiro-Wilk’s test will be used to assess the data distribution. For comparison of secondary efficacy outcomes, the Cochran–Mantel–Haenszel (CMH) test or Fisher’s exact test will be used to compare the categorical variables between two groups, while a t-test (normal distribution) or Mann-Whitney U test (non-normal distribution) is used to compare continuous variables, as appropriate. The incidence of AEs and drug-related AEs between the two groups will be compared using a chi-square test or Fisher’s exact test. In addition, the further interaction analysis across the subgroups, including age (65–79 years vs. ≥ 80 years), history of cardiovascular, renal, hepatic, and pulmonary diseases (yes vs. no), as well as interventional therapeutic endoscopic procedures (yes vs. no), will be carried out using a logistic regression model to adjust the study outcomes for above-mentioned potential confounding factors. All randomly assigned patients who receive at least one dose of the study medication will be included in the full analysis set (FAS) according to the intention-to-treat (ITT) principle, and at least one evaluable efficacy outcome is used for the analysis of all efficacy outcomes and baseline characteristics of patients. The safety set (SS), which includes all patients based on the “as treated” principle, will be used for the analysis of safety outcomes. Since the anticipated protocol violation will be uncommon and missing data will be supposed to be missing at random, the interim analysis or imputation for missing data are not performed in this trial.

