#### 2.2.1 Inclusion criteria

The inclusion criteria are as follows.

1) 65 years or older; 2) American Society of Anesthesiologists (ASA) physical status I to III; 3) body mass index (BMI) 18–30 kg/m^2^, and 4) scheduled for same-day bidirectional endoscopy under sedation.

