#### 2.2.2 Exclusion criteria

The exclusion criteria are as follows.

1) severe cardiovascular, pulmonary, renal, or hepatic disease; 2) previous hypotension (systolic blood pressure ≤90 mmHg), bradycardia (heart rate <50 beats/min), or hypoxemia (SpO2 <90%); 3) neurocognitive or psychiatric disorders; 4) contraindications to gastroscopy (gastric retention, long-term aspirin administration, etc.); 5) hypersensitivity to study medications; 6) drug or alcohol abuse; 7) definite upper respiratory tract infection; or 8) refusal to participation.

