Fospropofol is a water-soluble, phosphate ester prodrug, which can be metabolized by alkaline phosphatases to release liberated propofol after intravenous administration (Garnock-Jones and Scott, 2010). The released propofol from fospropofol binds to the γ-aminobutyric acid (GABA) receptor and thereby potentiates GABA-inhibitory synaptic currents to induce sedative effects (Garnock-Jones and Scott, 2010). A study of its pharmacodynamic/pharmacokinetic relationship in 12 healthy volunteers found that an intravenous bolus 10 mg/kg dose of fospropofola achieved propofol plasma maximum concentration of 2.2 mg/mLafter 8 (range 4–13) minutes, and reached the minimum mean MOAA/S score of 1.2 after 7 (1–15) minutes. Participants in this study completely recovered from sedation after 21–45 min following fospropofol administration (Bengalorkar et al., 2011). As a new sedative, fospropofol is expected to have the same sedative efficacy as propofol in elderly patients undergoing same-day bidirectional endoscopy, with a lower incidence of adverse reactions caused by hemodynamic and respiratory depression than that of propofol. On bassi of a phase II dose-response trial in patients undergoing colonoscopy, fospropofol 6.5 mg/kg was determined as the ideal dose, as no recorded episodes of deep sedation occurred during procedures under this dose (Cohen, 2008). In addition, both physicians and patients mostly preferred for fospropofol 6.5 mg/kg over the other doses (Cohen, 2008). In two clinical trials, fospropofol was shown to be safe and well tolerated at an initial dose of 6.5 mg/kg intravenously with supplemental doses as moderate sedation for elderly, obese, and high-risk patients in minor surgical procedures (Gan et al., 2010; Bergese et al., 2013). Fospropofol disodium for injection is a prodrug that is metabolized into propofol to produce a general anesthetic effect when administered intravenously. A phase 3 trial demonstrated that fospropofol disodium was not inferior to propofol for general anesthesia induction in American Society of Anesthesiologists (ASA) physical status I-II adult patients undergoing elective surgery and reduced the incidence of pain at the injection site (Wu et al., 2021). In addition, fospropofol’s slower onset should have less impact on patient’s hemodynamics compared to propfol, although it may potentially slow patient recovery (Gan et al., 2010). In clinical conditions where a more prolonged effect is desired and immediate onset of action is less important, fospropofol may have advantages over propofol. A pilot study has shown that fospropofol, administered in either an infusion/bolus or infusion-only regimen, is tolerable and effective for the short-term induction and maintenance of sedation in mechanically ventilated intensive care unit patients (Candiotti et al., 2011). These findings have prompted to exploration of fospropofol in providing sedation for elderly patients undergoing same-day bidirectional endoscopic procedures. However, the role of fospropofol sedation for same-day bidirectional endoscopy in elderly patients has not been fully determined. To our knowledge, this will be the first randomized controlled trial to assess the efficacy and safety of fospropofol sedation for same-day bidirectional endoscopy in elderly patients. In our patients, an initial bolus dose of fospropofol 6.5 mg/kg in combination with sufentanil 5 μg will be used for sedation induction, followed by supplemental doses of fospropofol 1.6 mg/kg as needed to achieve target sedation levels. This strategy will minimize the risk of oversedation and associated complications. Moreover, several confounding factors, which can influence the study outcomes, must be appropriately managed in this study to ensure that the reliable conclusions are obtaine. Subgroup analyses of the efficacy and safety assessments will be performed on basis of age, interventional therapeutic endoscopic procedures, history of cardiovascular, renal, hepatic, and pulmonary diseases.

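### The treatment-by-age interaction is tested only on a split at 80 years; if the effect changes steadily with age, this discards a large part of the available information

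*Protocol article*

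**What the plan says.** Section 2.10 specifies "the further interaction analysis across the subgroups, including age (65–79 years vs. ≥ 80 years", alongside history of organ disease and therapeutic procedures, and states that this "will be carried out using a logistic regression model to adjust the study outcomes". The Discussion extends it beyond the primary outcome: "Subgroup analyses of the efficacy and safety assessments will be performed on basis of age".

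Section 2.7 lists age among the data recorded before the procedure ("Demographic data [including age, sex, race, height, weight, and body mass index (BMI"). Section 2.2.1 admits patients from "65 years or older; 2) American Society of Anesthesiologists (ASA) physical status I to III" with no upper age limit. Section 2.2.2 excludes "severe cardiovascular, pulmonary, renal, or hepatic disease". Section 2.3 describes no stratification by age. The article gives neither an age distribution nor an expected number of patients aged 80 or older.

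**The concern.** The cut lies 15 years above the entry age, and nothing in the design enriches the group above it. The exclusion of severe organ disease plausibly thins that group further. The interaction would then rest on a contrast between a large group and a small one. All age differences between 65 and 79 are ignored, although the exact ages are in the data.

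What is at stake is how a null interaction would be read. With the split, it could be reported as evidence that the fospropofol–propofol comparison is consistent across age when the analysis had little chance of showing otherwise. This matters most for the safety outcomes, because the Introduction motivates the trial partly by the lack of safety data in elderly patients.

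**Working it through.** **1. The plan's own figure.** Section 2.9 gives a "non-inferiority margin (δ) of 8% in terms of the success rate", success of 95% in both groups, one-sided alpha 0.025 and 80% power. Per arm: (1.96 + 0.84)² × 2 × 0.95 × 0.05 / 0.08² ≈ 116.5, rounded up to 117, so 234 in total. This matches the article. After dropout, "a total of 256 patients (128 patients in each group) will be required for this trial". The article states no figure for interaction power or for patients aged 80 or older.

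**2. Information kept by the split.** With 1:1 allocation, the interaction information is N × p(1−p) × ¼ × the variance of the age term. If the log odds ratio is linear in age, the share of information kept by the indicator age ≥80 is the squared correlation between age and that indicator.

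The age distributions below are assumptions, all limited to 65–92 years. The last two columns apply step 5.

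| Assumed ages | Share ≥80 | Of 256 | Split keeps, steady trend | Age in years keeps, flat to 75 then rising | Split keeps, flat to 75 then rising |
|---|---|---|---|---|---|
| 65 + exponential, mean 4 | 2% | 6 | 0.31 | 0.51 | 0.74 |
| 65 + exponential, mean 5 | 5% | 12 | 0.43 | 0.62 | 0.78 |
| 65 + exponential, mean 6 | 7% | 18 | 0.50 | 0.69 | 0.79 |
| 65 + exponential, mean 8 | 12% | 32 | 0.59 | 0.76 | 0.81 |
| Normal (70, SD 5) | 3% | 7 | 0.19 | 0.51 | 0.57 |
| Normal (71, SD 5) | 4% | 10 | 0.24 | 0.57 | 0.60 |
| Normal (72, SD 6) | 10% | 26 | 0.42 | 0.70 | 0.71 |

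Under a steady trend the loss is 41% to 81%. Varying the shape and the upper age limit, with 6 to 32 patients aged ≥80, gives 38% to 85%. With 52 to 54 patients aged ≥80 (exponential mean 12; normal 75, SD 6) the loss is 34% to 45%. With ages spread evenly over 65–92 it is 26%.

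**3. Effect on power.** Take an interaction that age in years would detect with 80% power. Its power with the split is Φ(2.80 × √efficiency − 1.96).
- Efficiency 0.19: Φ(1.22 − 1.96) = 23%.
- Efficiency 0.59: Φ(2.15 − 1.96) = 58%.

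**4. By outcome.**
- *Outcome at about 30%* (the desaturation and hypotension rate in the Discussion), with 20 patients ≥80, an age SD of 5 and a 13-year gap in mean age, all assumed. The SE of the old–young interaction log odds ratio with the split is √(2/(10 × 0.21) + 2/(118 × 0.21)) = 1.02. With age in years it is 13/√(0.21 × 256 × 0.25 × 25) = 0.71. The 95% limits are a factor of about 7.3 and 4.0 either way.
- *Primary outcome at 5% failure.* Expected failures are 256 × 0.05 = 12.8 in all, and 0.3 to 1.6 among 6 to 32 patients aged ≥80. The chance that at least one arm has no failure at ≥80 is 1 − (1 − 0.95³)² = 98% with 6 patients, and 1 − (1 − 0.95¹⁶)² = 69% with 32.
- *A threefold change in odds ratio per 10 years.* Across four assumed age distributions, approximate power for the primary outcome is 11% to 28% with age in years and 5% to 19% with the split. For a 30% outcome it is 36% to 82% and 10% to 62%.

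**5. Sensitivity to shape.** If the effect is flat to 75 years and then rises steadily, age in years keeps 51% to 76% of the information and the split 57% to 81%. The split is ahead in all seven rows, by as little as 0.01. If the rise starts at 77.5, the figures are 29% to 65% and 75% to 79%.

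**The case against.** The strongest objection is that the gain depends on shape. A squared correlation is symmetric, so if the truth were a step at 80, age in years would lose the same 41% to 81%. Step 5 shows that a late rise also favours the split. A single curvature check has little power with so few patients in the tail, and an estimate at 80 years gains its precision by borrowing from younger patients through the assumed line. All of this stands. Age in years is better only if the trend begins before roughly 73 to 75 years, and the documents do not say which shape is true.

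A reader might take the Introduction and Discussion to show that the treatment effect changes with age. They report more adverse events in older patients. That is prognostic risk, not a changing difference between the drugs.

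A reader might also treat 6 to 32 patients as a known count. It follows only from the assumed distributions; no section gives the case mix.

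It can further be said that age bands are conventional and readable, and that an article may leave the reason for a cut-point, or a supplementary model, to a fuller document. That is fair, and the missing reason is not itself the finding. But the coding is stated in section 2.10, so the choice can be assessed.

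**Conclusion.** The point holds as a modest, inexpensive improvement to a supporting analysis. Assuming 2% to 12% of patients are 80 or older and a steady change on the logit scale, the split discards about 40% to 80% of the interaction information. With 50 or more such patients the loss is about 25% to 45%. A null result would be weak evidence of consistency across age.

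Three stronger readings are not supported:
- That a null interaction is close to guaranteed. Power under the split is 23% to 58% for an effect that age in years would detect with 80% power.
- That age is the trial's main effect-modification question. Section 2.10 lists it beside organ-disease history and therapeutic procedures.
- That the primary result is at risk. The non-inferiority conclusion does not use this analysis, and with about 13 expected failures the primary-outcome interaction is uninformative under either coding.

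The benefit is mainly for commoner safety outcomes, and even there the limits stay wide after the change.

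**What to change.** In section 2.10, make treatment × age in years the age-interaction analysis, linear with one check for curvature. Report the treatment effect with 95% CI at chosen ages, for example 70, 75 and 80. Keep the 65–79 and ≥80 results as a descriptive table with CIs and no test, and label the interaction exploratory.

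The cost is a sentence or two of analysis wording; no patients or data are added. The downside is the assumed smooth trend. A step at 80, or an effect flat until about 75 or later and then rising, would be picked up better by the split, which is why the table is kept.

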### 2.5 Efficacy assessments

#### 2.5.1 Primary efficacy outcomes

The success rate of the gastrointestinal endoscopy will be assessed according to the following criteria (Luo et al., 2022; Zhong et al., 2023): (1) completion of the gastrointestinal endoscopy; (2) no need for rescue sedative/anesthetic, which means the top-up doses of the experimental drugs will be administered no more than five times within any 15-min window from the initial administration to the end of the procedure.

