#### 2.5.2 Secondary efficacy outcomes

(1) Time to successful induction of anesthesia/sedation, defined as the time from the start of drug administration to the achievement of a MOAA/S score ≤1; (2) time to being fully alert, defined as the time from gastrointestinal endoscopy extraction or/and the time from the last drug administration to a MOAA/S score of five on three consecutive measurements; (3) time to discharge, defined as the time from the gastrointestinal endoscopy extraction or/and the time from the last drug administration to the initial occurrence of three consecutive Aldrete measurements of 9; (4) the top-up frequency and dosage of the study medications and sufentanil; (5) anesthesia/sedation satisfaction scores of the patients and endoscopists collected when the patients are ready for discharge.

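### Section 2.10 names logistic regression as the only model for the adjusted and subgroup analyses, but every secondary efficacy outcome is a time, count, dose or score

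*Protocol article*

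**What the plan says.** Section 2.10 first sets out unadjusted comparisons by outcome type: tests for proportions where the variable is categorical, and a t-test or Mann-Whitney test where it is continuous. It then adds "the further interaction analysis across the subgroups, including age (65–79 years vs. ≥ 80 years", together with organ-disease history and therapeutic endoscopy, and says that this analysis "will be carried out using a logistic regression model to adjust the study outcomes for above-mentioned potential confounding factors". No other regression model appears.

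The Discussion states the scope: "Subgroup analyses of the efficacy and safety assessments will be performed on basis of age, interventional therapeutic endoscopic procedures", followed by the disease-history factors. Efficacy and safety assessments are also the titles of sections 2.5 and 2.6, and section 2.5 contains both the primary and the secondary efficacy outcomes.

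The primary outcome in 2.5.1 is yes/no: "The success rate of the gastrointestinal endoscopy will be assessed according to the following criteria". The secondary outcomes in 2.5.2 are of other kinds. Induction time is "defined as the time from the start of drug administration to the achievement of a MOAA/S score ≤1". The next two items are "time to being fully alert, defined as the time from gastrointestinal endoscopy extraction" and "time to discharge, defined as the time from the gastrointestinal endoscopy extraction", each with a second possible starting point at the last drug dose. The remaining two are the frequency and dose of top-ups, and satisfaction scores.

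**The concern.** The article does more than leave the adjusted model open. It chooses one and gives it a scope that includes outcomes it does not fit. An analyst who followed 2.10 literally for time to full alertness would have to turn that time into a yes/no variable, with no threshold to use.

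Three things would then be at stake in the supportive analyses:

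- A threshold chosen after the data are seen is open to selection.
- An adjusted odds ratio for exceeding a threshold is not comparable with the unadjusted full-scale result in the same section.
- Cutting a continuous measure discards information.

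The outcomes concerned are not trivial. The Discussion accepts that recovery could be slower with fospropofol, and recovery is measured by two of these times. It also says that factors able to influence the outcomes need proper handling if the conclusions are to be reliable.

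**Working it through.** **1. Model against outcome**

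| Outcome (section) | Scale | Fits binary logistic regression as stated? |
|---|---|---|
| Endoscopy success (2.5.1) | yes/no | yes |
| Adverse events (2.6) | yes/no per patient | yes |
| Time to induction (2.5.2) | time | no |
| Time to fully alert (2.5.2) | time | no |
| Time to discharge (2.5.2) | time | no |
| Top-up frequency and dosage (2.5.2) | count, dose | no |
| Satisfaction (2.5.2) | score | no (an ordinal model would serve) |

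All five secondary efficacy items fall outside the named model. The article gives no cut-point for any of them.

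**2. The plan's own figure**

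Inputs from 2.9: success 95% in both arms, margin 8%, one-sided alpha 0.025, power 80%.

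n per arm = (1.960 + 0.842)² × 2 × 0.95 × 0.05 / 0.08² = 7.85 × 0.095 / 0.0064 = 116.5, rounded up to 117. That is 234 in total, as stated, so 117 per arm is used below.

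The article gives no SD, effect size, subgroup share or power for any secondary, adjusted or interaction analysis. Everything from here is therefore assumption: a normal outcome, a two-sided 0.05 test, and cut-points chosen only to show the range.

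**3. Adjusted treatment comparison, if the outcome were cut**

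The effect with 80% full-scale power is d = (1.960 + 0.842) × √(2/117) = 2.802 × 0.1307 = 0.37 SD.

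The relative efficiency of a cut at c, with share p above it, is φ(c)² / [p(1 − p)]. Power after the cut is Φ(2.802 × √efficiency − 1.960).

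- Median cut: efficiency 0.637, power Φ(0.28) = 61%. The two-proportion normal formula gives 60% and exact enumeration of the chi-square test 63%. The loss is about 17–20 points.
- 80/20 cut: efficiency 0.490, power Φ(0.00) = 50%, and exact enumeration also gives 50%. The loss is about 30 points. If the 20% share is fixed in the control arm, power is 54% or 44% depending on the direction of the effect.

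With 90% full-scale power (d = 0.42) the losses are about 17 and 28 points. Using 128 per arm and resetting d to the same full-scale power changes these figures by no more than about a point.

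**4. Treatment-by-subgroup interaction, if the outcome were cut**

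For a subgroup with share s, SE = √[2/(117s) + 2/(117(1 − s))]. Take an interaction as large as the main effect above, 0.37 SD. With s = 0.5, SE = 0.261 and full-scale power is Φ(0.366/0.261 − 1.960) = Φ(−0.56) = 29%. Cut outcomes use the efficiencies from step 3.

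| Subgroup share | Full scale | Median cut | 80/20 cut | Loss (points) |
|---|---|---|---|---|
| 10% | 13.1% | 9.9% | 8.5% | 3–5 |
| 20% | 20.1% | 14.3% | 12.0% | 6–8 |
| 30% | 24.9% | 17.5% | 14.4% | 7–11 |
| 50% | 28.8% | 20.0% | 16.4% | 9–12 |

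If the interaction were twice as large (0.73 SD) with equal subgroups, power would go from 80% to 61% (median cut) or 50% (80/20 cut).

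**The case against.** The best reply is that the sentence was never meant for the continuous outcomes. Success and adverse events are already an efficacy and a safety assessment. The same section gives continuous variables a t-test or Mann-Whitney test, and nothing says that a time or score will be cut. An ordinal logistic model would take the scores without a single threshold. The model for each secondary outcome in a supportive analysis is also something that an article often leaves to a fuller document.

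Much of this stands. A reader might infer that the plan commits to dichotomising its secondary outcomes, but no sentence says so. A reader might also infer that the trial gives up power to detect slower recovery. It does not: the overall difference in recovery time is tested on its full scale, and the logistic analysis is an addition to that. Nor can a loss of 15–30 points be given as a property of this plan. For an interaction test it takes an interaction about 1.5 to 2 times the 0.37 SD effect in a fairly large subgroup.

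What does not stand is that this is a mere omission. Section 2.10 names a model and attaches it to the study outcomes without limit, and the Discussion repeats the wide scope. If only binary outcomes were meant, the article needs to say so.

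**Conclusion.** The point holds as a mismatch between the stated model and the outcomes it is stated to cover. It is limited to the supportive adjusted and subgroup analyses of the 2.5.2 outcomes. The primary non-inferiority test, the unadjusted full-scale secondary comparisons, and the use of logistic regression for success and adverse events are untouched by it.

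The power losses are conditional on a dichotomisation that the article does not announce, and on an assumed normal outcome, assumed effects and assumed cut-points. The interaction figures are the more relevant ones, because the sentence in 2.10 is mainly about interaction. They also show that these tests would be weak at that effect size even on the full scale. The firmer reason to act is the unstated cut-point and the change of question between the unadjusted and adjusted results.

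**What to change.** In 2.10, restrict logistic regression to the binary outcomes, endoscopy success and adverse events. For the other outcomes, state:

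- times and doses: a linear model on the full scale, with times log-transformed;
- satisfaction scores: a linear or an ordinal model;
- number of top-ups: a count model, such as Poisson or negative binomial.

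Each model should contain treatment, subgroup and treatment-by-subgroup terms, and the interaction estimate should be reported with its 95% CI. If adjusted and subgroup analyses are intended only for the binary outcomes, say that instead and bring the Discussion into line.

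The cost is one or two sentences and a little extra analysis work. No new data are needed, and the sample size and primary analysis do not change.
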